### Outcomes

While traditional evaluations of interventions define one primary outcome, complex interventions, such as this, have increasingly defined multiple primary outcomes that are equally important [19–21]. The primary and secondary outcomes are detailed in Table 1 with questionnaire items used to evaluate outcomes, an example per outcome, and hypothesized direction of change. The trial has three primary outcomes:Past year experience of physical IPV amongst currently married womenPast year experience of severe physical IPV amongst currently married womenWomen’s past week depressive symptoms

**Table 1 Tab1:** Primary and secondary outcomes for the trial

	Number of items and origins	Example question and response categories	Scaling	Alpha	Hypothesized direction
Primary outcomes					
Past year experience of physical IPV amongst currently married women	Five items ask about married women’s experience of physical IPV. The scale is based on the WHO’s multi-country study of IPV [25].	(Q) In the past 12 months how many times has your husband hit you with a fist or with something else which could hurt you? (A) Never, once, few, many	A positive response to one or more items coded as yes		Decrease
Past year experience of severe physical IPV amongst currently married women	Same scale as above. Severe physical IPV is defined as experiencing more than one item of the five, or experiencing any one item more than once, creating a dichotomous measure equivalent to more than once experiencing physical IPV.	(Q) In the past 12 months how many times has your husband slapped you or thrown something at you which could hurt you? (A) Never, once, few, many	Two or more items responded to as ‘once’ or responding to any single item as “few”, or “many”.		Decrease
Women’s past week depressive symptoms	Depressive symptoms are assessed using the Center for Epidemiological Studies Depression scale (CES-D), comprising 20 items asking about depressive symptoms in the past week [26].	(Q) During the past week I had crying spells (A) Rarely or none of the time; some or little of the time; moderate amount of time; most or all of the time	Mean score created; higher mean’s more depressive symptoms	0.90	Decrease
Secondary outcomes					
Household Food Insecurity in past 4 weeks	Three items comprising the Household Hunger Scale, developed for global use and comparability [27].	(Q) In the past 4 weeks, how often was there no food to eat of any kind in your house because of a lack of money? (A) Never, Rarely, Sometimes, Often	Mean score created; higher indicates more food insecurity	0.94	Decrease
Financial shock resilience	One item asks about ability to mobilise money in an emergency. This measure was developed for use in South Africa, and has been used in Asia.	(Q) If you had an emergency at home and needed 500 Afghani, how easy would you say it would be to find the money? (A) Very easy, fairly easy, somewhat difficult, very difficult	Recoded into binary of very or fairly easy and somewhat difficult or very difficult		Decrease
Women’s monthly income	A single item asks about earnings in the past month.	(Q) Considering all the money you earned from jobs or selling things, how much did you earn last month?	Mean		Increase
Women’s total savings	A single item asks women the total value that they have in savings.	(Q) How much money have you got in savings?	Mean		Increase
Life satisfaction	Life satisfaction is assessed using four-items derived from the Satisfaction With Life Scale [28]. This has been used across South Asia [29].	(Q) In most ways my life is close to my ideal (A) Strongly agree, agree, disagree, strongly disagree	Mean; higher means less satisfied	0.90	Decrease
Past four week suicidal ideation	A single item assesses thoughts of suicide in the past month, with a binary response possible.	(Q) In the past four weeks, has the thought of ending your life been in your mind? (A) Yes, No	Binary yes/no		Decrease
Women’s gender attitudes	This scale was developed locally from discussions with Afghan’s before being tested in Pakistan. A series of 11 questions ask about gender attitudes that individual women hold.	(Q) I think it is a good thing for a young wife in my family to be beaten to teach her how to behave properly (A) Strongly disagree; disagree; agree; strongly agree	Mean score; higher score indicates less gender equitable attitudes	0.87	Decrease
Married women’s participation in household decision making	Five items are asked about women’s ability to participate in household decisions, based on the WHO Multi-Country Study on Domestic Violence [25].	(Q) In the last three months, how often your views been listened to on matters concerning the children and their schooling or work in your home? (A) Never; sometimes; often	Mean score; higher scores indicate more participation	0.77	Increase
Past year emotional IPV amongst currently married women	Seven items ask about experiences of emotional abuse by the husband.	(Q) In the past 12 months how many times has your husband insulted you or made you feel bad about yourself? (A) Never; once; few; many	Mean score; higher score indicates more emotional violence		Decrease
Perceptions of husband cruelty amongst currently married women	Five items ask about married women’s perceptions of her husband and his attitudes and relationship towards her.	(Q) My husband is very strict and controlling. (A) Strongly disagree; disagree; agree; strongly agree	Mean score: higher scores indicate more cruelty	0.88	Decrease
Mother in law and sibling abuse:	Two items: A single item assesses whether mother-in-laws have hit the woman in the past 12 months and another item assesses whether siblings have hit the woman in the past 12 months, an affirmative response to either item would indicate abuse.	(Q) In the last 12 months were you slapped, hit or beaten by your mother-in-law?. (A) Never, sometimes, often	A positive response to one or both items coded as yes		Decrease
Perceptions of mother-in-law cruelty.	For married women who currently live with their mothers-in-law, six items ask about their relationship and the mother-in-law’s attitudes towards her.	(Q) My mother-in-law can frighten me (A) Strongly disagree; disagree; agree; strongly agree	Mean score: higher scores indicate more cruelty	0.84	Decrease

The secondary outcomes for the study reflect the multiple objectives of the intervention and fall into four categories: economic outcomes; mental health and wellbeing; gender attitudes, and power and violence outcomes.

Secondary economic outcomes are:Past four week household food insecurity;Financial shock resilience;Women’s past month earnings; andWomen’s total savings.

Secondary mental health and wellbeing outcomes are:Current life satisfaction; andPast four week suicidal ideation.

Secondary gender attitudes, and power and violence outcomes are:Women’s gender attitudes;Past year emotional IPV amongst currently married women;Perceptions of husband cruelty amongst currently married women;Past year mother-in-law and sibling abuse; andPerceptions of mother-in-law cruelty amongst currently married women.

### Data collection

Quantitative data were collected through face-to-face structured interviews using paper and pencil by trained female fieldworkers. Questionnaires were translated from English into Dari and Pashto through a process of translation and back translation, and piloted by the fieldwork team. Data collectors conducted individual interviews with women in private locations.

The participant timeline is set out in Fig. 2. Baseline data collection was completed between October 2016 and February 2017. Follow-ups are 12 months and 24 months after baseline.

**Fig. 2 Fig2:**
[figure not shown]
Evaluation flowchart

### Assignment of interventions

Women were individually randomized into the intervention and control arms. Assignment of women into the intervention and control group was done through women drawing coloured balls from an opaque bag or box after enrollment into the study.

While interventions such as this are often randomized at the cluster (village) level into intervention and control arms to avoid contamination [22], pilot work showed that women may mix in public places but did not tend to talk about the types of things covered by the WfWI programme. Given the intensive education content and focus on skills building, we determined that significant contamination was unlikely. Given the levels of insecurity in Afghanistan, this methodology reduced the number of villages where access and research would have to be negotiated, reducing security risks. Randomisation occurred on the day after recruitment (two villages) or at the time of recruitment (all other villages).

In one village, WfWI ran its men’s engagement programme, as detailed above. Villages are not randomized to receive this: it is provided in villages where it is perceived work would be difficult without buy-in from the men in the community.

### Data management and analysis

Questionnaires were double-entered into SPSS, discrepancies between the entered data were identified, and answers were verified through checking the paper questionnaires and corrected. The same process will be undertaken for both follow ups.

The data will be cleaned by the study statistician. One dataset will be compiled for analysis of key variables based on the three data collections: baseline, follow up at the end of the programme (12 months from baseline), and follow up 12 months after programme graduation (24 months from baseline). The data will be described by presenting frequencies for categorical variables and means for scale and sub-scales, with 95% confidence intervals by study arm.

The main analysis for outcomes of intimate partner violence will be conducted on a sub-set of the sample who are currently married at endline. For depression, it will be conducted on the entire sample. Intention-to-treat (ITT) analyses will be conducted. A *per protocol* analysis will also be conducted as a secondary analysis (i.e. including just those women who attended more than 75% of WfWI’s core programme). Cross tabulation and chi-square tests will be used to determine whether there are differences in demographics between the treatment and control group. The primary analysis will be carried out by fitting Generalized Linear Mixed Models (GLMMs) with a term for treatment arm [23]. For outcomes using scales, the difference in the scores between baseline and 12 months, and baseline and 24 months will be assessed. For each of the scales, a linear mixed model will be fitted with fixed terms for treatment arm. The scores will be directly calculated from the component items, while the scales will combine the items using weights determined by carrying out a principal component analysis on the items at baseline, and using the loadings for the first principal component as the weight for each item. These analyses will firstly be carried out on the ITT population and then repeated for the per protocol population.

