### Trial design

The study is a two-arm, individually randomized controlled trial. Intervention arm participants receive the WfWI intervention (i.e. WfWI’s core programme), a combined social empowerment and livelihoods strengthening intervention, alongside a US$120 cash transfer over 12 months (US$10 per month). This cash transfer is a standard part of WfWI’s core programme to cover training-related expenses, contribute to household needs and help women to start to build savings. Control arm participants are given $10 per interview to motivate assistance in the study and as reimbursement.

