### Sample size

A pilot study was conducted in August 2016 with 100 women who were already part of the WfWI intervention to assess the questionnaire, as well as provide an estimate of physical IPV experience in the past 12 months. We found many of the women already enrolled in the WfWI intervention were not currently married, in fact only 37/100 were. Among these, past year physical IPV prevalence was 32.4% and past year severe IPV prevalence was 27%. At the time, this corresponded to published data, which estimated 39.3% of women had experienced past year physical IPV [16].

We used an assumption of seeing an effect size of 0.3 difference between the 12 month prevalence of physical IPV at endline in the control and intervention arms. This is the effect size seen in several recent evaluations of effective violence prevention interventions [18, 19]. We assume that the 12 month control arm IPV prevalence will be 32% and severe IPV 27%. Using Stata, with power set at .80 and alpha at 0.05, sample size per arm was estimated to be 337 for past year physical IPV, and 422 for past year severe physical IPV. Based on our calculations for the percentage of women recruited into the intervention being currently married, and the potential loss to follow-up, the target number of participants was 1477.

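### The secondary per-protocol set is defined by attendance at a programme only one arm receives, so its arm contrast is either not estimable or no longer randomised

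*Protocol article*

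**What the plan says.** All of the analysis text is in the protocol article, Data management and analysis. The main analysis is by randomised arm: "Intention-to-treat (ITT) analyses will be conducted". A per-protocol "analysis will also be conducted as a secondary analysis", and its population is described as "including just those women who attended more than 75% of" the core programme. No rule is given for how control women enter that population.

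The main model is specified as "fitting Generalized Linear Mixed Models (GLMMs) with a term for treatment arm", with linear mixed models carrying an arm term for the scales. No baseline or village covariate is named. The section closes: "These analyses will firstly be carried out on the ITT population and then repeated for the per protocol population".

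The Trial design section says what each arm gets. "Intervention arm participants receive the WfWI intervention", together with the monthly cash transfer. For the other arm: "Control arm participants are given $10 per interview to motivate assistance in the study and as reimbursement". No sessions are described for control women.

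**The concern.** The article states the population rule, the threshold and the model, and together they do not give a usable treatment comparison. Applied as worded, the rule selects from one arm only, while the model needs both. The natural repair is to compare intervention women above the cut-off with all controls, but this conditions on something that happens after randomisation in one arm and not in the other.

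The article itself gives reasons to think attendance is not random with respect to the outcome. Family support for taking part could not always be secured (Eligibility criteria). Women's freedom of movement is limited, and husbands' controlling behaviour is listed as a risk factor for spousal violence (Background). Sustained attendance over a year may therefore be related to IPV.

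What is at stake is a secondary result printed beside the ITT estimate and easily read as the effect in women who really took part. In this form it could mix programme effect with selection, in an unknown direction.

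**Working it through.** **1. Who can be in the set.** There are 747 intervention and 714 control women (Limitations), of whom 481 and 454 were currently married at baseline (Table 2). Under the design as described, control women have no sessions to attend. So 0 of 714 controls (0 of 454 married) can meet the rule. With one arm empty, the arm coefficient is not estimable.

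**2. The planned effect, as a yardstick.** The Sample size section assumes 32% control prevalence of physical IPV, an effect size of 0.3, power 0.80 and alpha 0.05, and reports 337 per arm. Reading 0.3 as a relative reduction gives 0.32 × 0.7 = 0.224. With n = [1.96√(2p̄q̄) + 0.842√(p₁q₁ + p₂q₂)]² / (p₁ − p₂)² and p̄ = 0.272:

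- numerator: (1.96 × 0.6293 + 0.842 × 0.6256)² ≈ 3.098
- divided by 0.096² = 0.009216, this gives about 336.1, so 337.

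The stated figure is reproduced, and the planned effect is 32 − 22.4 = 9.6 points.

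**3. Attenders against all controls when there is no true effect.** Let a be the share attending more than 75%, and let p_att and p_non be the risks in attenders and non-attenders. By randomisation the control risk is a·p_att + (1 − a)·p_non. The spurious difference is then

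p_att − [a·p_att + (1 − a)·p_non] = −(1 − a)(p_non − p_att).

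The documents give neither a nor the gap. Assuming a from 0.6 to 0.8 and a gap of 7 or 12 points:

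| a | gap 7 points | gap 12 points |
|---|---|---|
| 0.6 | 0.4 × 7 = 2.8 | 0.4 × 12 = 4.8 |
| 0.8 | 0.2 × 7 = 1.4 | 0.2 × 12 = 2.4 |

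The size is 1.4 to 4.8 points, or 15% to 50% of 9.6. The sign follows the gap. If non-attenders are at higher risk, the programme looks better than it is; if attenders are, it looks worse; with no gap the difference is zero.

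**4. The same calculation anchored at 32% overall.** Let non-attenders have r times the attenders' risk, so p_att = 0.32 / [a + (1 − a)r].

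- a = 0.8, r = 1.5: 0.32/1.1 = 0.291, which is 2.9 points too low.
- a = 0.6, r = 1.5: 0.32/1.2 = 0.267, which is 5.3 points too low.
- a = 0.8, r = 1/1.5: 0.32/0.9333 = 0.343, which is 2.3 points too high.
- a = 0.6, r = 1/1.5: 0.32/0.8667 = 0.369, which is 4.9 points too high.
- r = 1: no difference.

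With 481a attenders against 454 controls, a normal-approximation test at two-sided 5% would reject about 15% of the time in the first case, 34% in the second, and 5% when r = 1. These use baseline married numbers with no loss to follow-up.

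**5. What an instrumental-variable estimate does.** With no attendance in controls, the complier average causal effect is the ITT difference divided by a. Any dose version is the same ITT difference divided by mean attendance. Both rescale one contrast, so a dose version cannot test whether attendance below 75% has an effect; it assumes linearity instead. The threshold matters. If the ITT difference were the planned 9.6 points and 60% passed the 75% cut-off, the estimate would be 9.6/0.6 = 16.0. If 80% attended at all and that were the cut-off, it would be 9.6/0.8 = 12.0.

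**The case against.** The strongest reply is that the literal reading is uncharitable. Repeating models with an arm term makes sense only if controls are retained, and the parenthesis is shorthand for adherence in the arm that has something to adhere to. A condensed article may leave the handling of controls to a fuller plan. This is fair as far as it goes: the empty control arm is probably a gap in wording, not what the authors mean to run. It does not rescue the analysis, because the charitable reading is the one that filters a single arm after randomisation, and the article describes no adjustment for that.

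A reader might infer that the analysis will exaggerate benefit because women in controlling households drop out of the intervention arm. The documents do not support that as a statement of fact. The remark on family support concerns involvement in general, not attendance. Other text points away from it: women had to be willing to attend all classes (Eligibility criteria), demand was very high, and some male relatives were angry that women had not been registered (Challenges). Selection is plausible; its direction is not established.

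A reader might also infer that the trial's main conclusion is at risk. It is not: the per-protocol analysis is expressly secondary and the ITT analysis does not depend on it.

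**Conclusion.** The point holds as a defect in a secondary analysis. Taken literally, the per-protocol contrast has no comparator; taken charitably, it is a non-randomised comparison that the article does not identify as such. Both follow from the text without any assumed figure.

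The size of the problem does not follow from the text. The illustration of 1.4 to 4.8 points in either direction, against a planned 9.6, rests on assumed attendance of 60-80% and an assumed 7-12 point risk gap. If attendance is unrelated to risk, there is no bias. Importance is moderate: the change should be made before analysis, but no primary result or sample-size figure turns on it.

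**What to change.** Replace the attender-only contrast with a complier average causal effect analysis, using randomised arm as the instrument for attending more than 75%. Alternatively, keep the contrast, state how control women enter it, label it as non-randomised and report the complier analysis beside it.

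- Keep all randomised women in the ITT analysis set for each outcome: those currently married at endline for IPV, and the whole sample for depressive symptoms. Use the same model terms as the ITT analysis.
- State the exclusion assumption openly. Women below the cut-off may still gain from partial training, cash transfers, savings groups or referrals (Intervention section). If so, the 75% estimate is inflated.
- Show sensitivity to a lower threshold, for example any attendance. Present any dose version as resting on linearity, not as a test of exclusion.

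The cost is wording. No change in sample size is needed, and attendance data are implied by the 75% rule, although the article does not say outright that they are recorded. The price is a wider interval and an assumption that the data cannot verify.

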Component 2: Skill Building: the sessions that fall under skill building are delivered through hands-on training and practice over the year-long programme and focus on building basic skills in:Numeracy. This is provided for women who need it so that women can learn to count, add/subtract, and use money. All women participants in Afghanistan receive this component.Basic business skills. Women learn and practice basic business skills needed for self-employment, group businesses or employment. It covers bookkeeping, selling, planning and marketing their products, and is followed by three sessions on cooperatives looking at the benefits and different types of cooperatives including their structures.Vocational skills. WfWI conducts market assessments to identify the best income generation activities for women, given their resources, education and other constraints. Specific training in Afghanistan is focused on animal husbandry, tailoring, gardening and knitting.

Component 3: Resource provision: To complement the informational training and skill building, women receive financial support, referrals and opportunities for saving through the 12 months:Women receive a monthly conditional cash transfer of US$10 per month (total received US$120). There is no stipulation about how women should spend this month. Some women choose to save this money to help them establish their own businesses. Others use it to cover basic needs such as food, clothing and medicine.WfWI provides women participants with a range of referral services. A list of referral services is developed. Where women need additional support, they are referred through to services.In Afghanistan, WfWI has introduced an adapted version of the Self-Help Group, an informal grouping of women who set up a small ‘bank’ in which they save together. This is not a compulsory savings programme, but many groups decide to start them as part of the programme.

Component 4: Connections to other women, local women’s networks and global supporters: Women go through the programme in classes of 25 and begin the programme with the same group with whom they graduate. This provides a safe space for socially excluded women to learn new skills, share experiences and receive support.

Women for Women International also runs a range of complementary programmes to promote sustainable change and a supportive, enabling environment for women.

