### Limitations

The study has a number of limitations, primarily linked to the wider challenges of operating in a conflict/post-conflict setting. Due to the challenges with recruitment and randomization at the start of the process, there are slightly more participants in the intervention arm (*n* = 747) compared to the control arm (*n* = 714). Despite this, the randomization was effective in achieving balance in socio-demographic measures across arms. The decision to randomize at the individual level, rather than the cluster level may have an impact. The concern remains that there could be some information diffusion from those in the intervention to those in the control group. WfWI had previously worked in two of the villages so there is some possibility that there could already be spillover effects in these villages, which may impact results.

We were advised not to include questions which might be considered offensive or very embarrassing for women. Therefore, we did not ask about sexual violence even though sexual violence in prevalent in Afghanistan [15] and measures of IPV include sexual violence in other settings. The low level of past-year sexual IPV reported in the Afghan DHS somewhat supports our decision, as it suggests that the notion was either hard to interpret culturally or particularly embarrassing for women to report.

Finally, while the study is currently operating, the ongoing security challenges of working in Afghanistan remain paramount. Depending on the wider political situation, this may reduce programming intensity and also lead to challenges around follow-up of participants.

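### The sample size makes no allowance for the fixed classes of 25 in which only the intervention arm is taught, and the named mixed models do not say that class is a random effect

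*Protocol article*

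**What the plan says.** All points are in the protocol article; the statistical analysis plan is not shown.

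- **Sample size.** The inputs are "We assume that the 12 month control arm IPV prevalence will be 32% and severe IPV 27" per cent, "with power set at .80 and alpha at 0.05", and an effect size of 0.3. The result is "sample size per arm was estimated to be 337 for past year physical IPV, and 422 for past year severe physical IPV". The target of 1477 then adds an allowance for the share of women currently married and for loss to follow-up. No ICC or design effect is mentioned.
- **Intervention, Component 4.** "Women go through the programme in classes of 25 and begin the programme with the same group with whom they graduate".
- **Assignment of interventions.** Women are randomised individually, in sessions held village by village. Clustering is discussed only as a question of contamination between arms.
- **Data management and analysis.** "The primary analysis will be carried out by fitting Generalized Linear Mixed Models (GLMMs) with a term for treatment arm". Scale outcomes get a linear mixed model, again with only the arm term named. Neither model is given a grouping factor.
- **Outcomes.** There are three primary outcomes: past-year physical IPV and past-year severe physical IPV, both among currently married women, and depressive symptoms on the CES-D scale among all women.

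**The concern.** Individual randomisation makes the arms comparable at the start, but it does not keep women independent afterwards. Intervention women spend a year with the same classmates. They are taught through discussion and role-play, and many groups start saving together. Peer support is one of the programme's components, so some similarity of outcome within a class is to be expected. Controls have no such grouping. The trial is therefore partially nested, with clusters in one arm only.

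Two things follow if class is left out. The variance of the intervention-arm mean is understated, so p-values are too small and intervals too narrow. The trial also has less power than the sample-size section states. Depressive symptoms are the most exposed primary outcome, because the whole class contributes to that analysis rather than only its married members.

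**Working it through.** **1. Reproducing 337 and 422.** The control prevalences are 32% and 27%. The 0.3 is read as a 30% relative reduction, giving 22.4% and 18.9%. An absolute difference of 0.3 would need only 24 per arm at 32% and is impossible at 27%. Alpha is 0.05, taken as two-sided, and power is 0.80. The formula for independent women, without continuity correction, is

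n = [1.96·√(2p̄(1−p̄)) + 0.8416·√(p₁(1−p₁)+p₂(1−p₂))]² / (p₁−p₂)²

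- Physical IPV: [1.96·0.6293 + 0.8416·0.6256]² / 0.096² = 336.1, rounded up to 337.
- Severe IPV: [1.96·0.5947 + 0.8416·0.5919]² / 0.081² = 421.9, rounded up to 422.

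Both stated figures are matched exactly, so they contain no design effect.

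**2. Class sizes.** The intervention arm has 747 women, and 747/25 is about 30 classes if classes consist of trial women. Of these 747, 481 are currently married at baseline, so a class holds about 25 × 481/747 = 16 married women. Hence m = 16 for IPV and m = 25 for CES-D.

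**3. Design effect, intervention arm only.** DE = 1 + (m−1)·ICC. The ICC is an assumption.

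| ICC | DE, m = 16 | DE, m = 25 |
|---|---|---|
| 0.01 | 1.15 | 1.24 |
| 0.02 | 1.30 | 1.48 |
| 0.05 | 1.75 | 2.20 |

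**4. Two-sided error if class is ignored.** The true variance exceeds the assumed one by R = (DE/n_I + 1/n_C)/(1/n_I + 1/n_C), and the error is 2·[1 − Φ(1.96/√R)]. The arms are 481 and 454 for IPV, and 747 and 714 for CES-D.

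| ICC | R, IPV | error, IPV | R, CES-D | error, CES-D |
|---|---|---|---|---|
| 0.01 | 1.073 | about 5.9% | 1.117 | 6.4% |
| 0.02 | 1.146 | 6.7% | 1.235 | 7.8% |
| 0.05 | 1.364 | 9.3% | 1.586 | 12.0% |

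**5. Power with class allowed for (m = 16).** Power = Φ{(p₁−p₂)/√[p₁(1−p₁)/n_C + DE·p₂(1−p₂)/n_I] − 1.96}. For severe IPV at 422 per arm and ICC 0.02, the standard error is 0.03065, so power = Φ(0.081/0.03065 − 1.96) = Φ(0.683) = 75%.

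| ICC | severe IPV, 422 per arm | severe IPV, 481 and 454 | physical IPV, 337 per arm | physical IPV, 481 and 454 |
|---|---|---|---|---|
| 0 | 80% | 84% | 80% | 91% |
| 0.01 | 78% | 82% | 78% | 89% |
| 0.02 | 75% | 79% | 75% | 88% |
| 0.05 | 68% | 73% | 68% | 82% |

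The columns with 481 and 454 assume that all 935 women married at baseline are followed. Severe IPV needs 2 × 422 = 844, and 844/935 = 0.90, so a loss of about 10% uses up that margin.

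**6. Size needed for 80% power (m = 16).** At ICC 0.01, 0.02 and 0.05, severe IPV needs 447, 475 and 557 per arm instead of 422. Physical IPV needs 356, 378 and 445 instead of 337.

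**The case against.** **The model may already handle this.** A mixed model has at least one random effect by definition. The article leaves it unnamed, and it could be class. A journal article commonly leaves such detail to the analysis plan. This stands: a reader might infer that the stated model treats women as independent, but the text does not say so, and naming the arm term does not exclude others. The error rates in step 4 therefore describe what happens if class is left out, not what the article commits to. The sample size is different. It is a finished calculation whose inputs and inflation factors are listed, and an unseen plan cannot put a class allowance into it.

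**The size is conditional.** No ICC is given, and at zero nothing changes. At 0.01 the loss of power is about two points. That classes consist only of trial women is also an assumption; fewer trial women per class would mean a smaller design effect. All of this stands, so a flat statement that the power and the intervals are wrong would go too far.

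**Village.** A reader might go further and infer a biased effect estimate if village is omitted, because randomisation was done in separate village sessions, "there are slightly more participants in the intervention arm", and the Background quotes IPV of 6% to 92% by province. The documents do not support that. No allocation by village is reported. The split of 747 to 714 is compatible with chance under 1:1 allocation (exact binomial p = 0.40). The 6% to 92% range is lifetime IPV, with its extremes in provinces outside the trial, which ran only in Kabul and Nangarhar. With women randomised within villages, omitting village mainly costs precision and tends to make standard errors too large, the opposite direction to omitting class.

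**Conclusion.** The point holds in a limited form. The sample size assumes independent women although the design groups one arm into fixed classes, so the stated 80% power is correct only for a class ICC of zero. The analysis section leaves open whether class enters the model, and only a class effect would protect the test.

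Over an assumed ICC of 0.01 to 0.05, the consequence runs from minor to material. With class ignored, the error is about 5.9% to 9.3% for IPV and 6.4% to 12.0% for CES-D. Severe-IPV power at the planned size is about 78% down to 68%. With every woman married at baseline followed, it is about 82% down to 73%, before losses. Physical IPV has more room: on the same basis it stays above 80% across this range. These figures rest on the assumed ICC, on classes made up of trial women, on about 16 married women per class, and on marital status at baseline standing in for status at endline.

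**What to change.** 1. In the analysis section, or in the analysis plan if it does not already do so, specify a partially nested model for the primary outcomes: a random effect for class in the intervention arm only, with a small-sample degrees-of-freedom correction because there are only about 30 classes.
2. Restate the power for the IPV outcomes over a stated ICC range, applying DE = 1 + (m−1)·ICC to the intervention arm, and say what m and ICC were assumed.
3. Optionally add village as a fixed effect for precision, since women were randomised within villages.

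Recruitment is complete, so item 2 changes what is reported and not the number of women. The cost is slightly wider intervals, a lower stated power, and the work of linking class membership to the trial data. The article plans an analysis of women who attended more than 75% of the programme, so attendance must be recorded in some form, but it does not say that class membership is held in the dataset. This should be confirmed before the model is fixed.
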